**2.2** **Secondary objectives**

- Compare the number and severity of rejection episodes in the pancreas allograft to the ones occurring in the kidney allograft (SPK), and the ones diagnosed by the duodenal segment biopsies.
- Compare pancreas graft survival at 12, 36 and 60 months after transplantation between the prospective study group and retrospective control group.
- Monitor kidney (and pancreas) graft survival (SPK) 12, 36 and 60 months post-Tx.
- Compare patient survival at 12, 36 and 60 months post-Tx.
- Compare the incidence of non-surgical complications (infections,cardial complications, pulmonary complications and neurological complications).
- Explore if potentially graft devastating complications in pancreas transplants can be detected earlier with the microdialysis method than by current standard of care
- Explore if new complication specific biomarkers can be detected by the microdialysis method

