**2.7 Pancreas transplant monitoring with microdialysis catheters**

- At end of surgery totally three microdialysis catheters will be inserted. The catheters membranes have a 100 kDa pore size, an outer diameter of 0.6 mm and a length of 30 mm. A secure thread is positioned 60 mm from the tip (CMA 65, CMA Microdialysis AB, Stockholm, Sweden).The left abdominal wall will be punctured at three different locations close to each other by a hypodermic needle (Sterican® 14G X 3 1/8 “, B. Braun AG, Melsungen, Germany) through which the microdialysis catheter will be led. After removing the hypodermic needle one microdialysis catheter will be sutured to superfluous connective tissue on the pancreas graft, one will be sutured to the fascia of the right psoas muscle implying that the pancreas graft will be in direct contact with the catheter, and one catheter will be secured close to the duodenoduodenostomy. The catheters will be secured to the skin using a 4.0 thread. Each catheter will be perfused with 6 % hydroxyethyl starch at a rate of 1 µL/minute by microinjection pumps (CMA 107, CMA Microdialysis AB, Stockholm, Sweden), and the samples will be collected in microvials (CMA Microdialysis AB, Stockholm, Sweden)
- Postoperatively the microdialysis samples will be analyzed every second hour at the bedside for glycerol, glucose, lactate, and pyruvate using a microdialysis analyzer (Iscus Flex, CMA Microdialysis AB, Stockholm, Sweden).The lactate to pyruvate ratio will be calculated. Thereafter the samples will be frozen to -20°C and later to -80°C.
- Since this study is the first of its kind and threshold values for detecting e.g. pancreatic graft ischemia, leakages, and rejections have not been established we will not implement e.g. a decision tree in the protocol. However, since not only the physicians responsible for the studies, but also the nurses at ward have substantial experience with the microdialysis method, we expect that deviations from the normal course may lead to prescription of e.g. ultrasound Doppler examinations, and that graft complications thereby may be detected earlier. From a purely scientific point of view one could argue that blinding nurses and physicians for the results would be appropriate. However, we consider this not feasible since the researchers also are responsible for treating the patients and it is important that they have immediate access to the data to reveal e.g. inappropriate sampling.

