- The catheters will be left in situ for as long as they are able to sample appropriately, or until the patient is dismissed. The patient may at any time point request removal of the catheters. In our liver studies the patients had well-functioning catheters for a median of 10 days. The catheters are easily pulled out after loosen the skin secure. According to our experience from the liver- and Whipple studies removing the catheters is not associated with any risk or pain. After study completion the samples will be thawed and analyzed en bloc for a wide range of inflammatory mediators including complement factor 5 a and the chemokine CXCL-10, which were specific biomarkers for ischemia and rejection respectively in our previous liver study. These analyses will be performed in [name] lab in the Department of Immunology at our hospital. We will also consider analyzing samples for presence of various micro-RNAs.

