**10.3 Statistical methods in data analysis**

- The primary evaluation criteria ‘Incidence of rejection’ and ‘Rate of surgical complications’ will be evaluated for several populations:

- All patients who receive at least one dose of study medication, defined as the ‘Intention-to-Treat’ population.

- All patients who complete 12 months of intended study medication, defined as the ‘Intention completed’ population.

The analysis of these categorical parameters will consist of:

1. Comparisons of groups using the Fisher exact test.

2. Confidence intervals of 95% of the percentage of incidence of these

events.

- The loss of grafts and deaths will be analysed by the Kaplan-Meier method for estimating the time to events.
- Continuous (non-categorical) variables will be analyzed by student t-tests and chi-square tests.
- Microdialysis data are typically non-normally distributed. We will therefore use the Wilcoxon Signed rank test for repeated measurements and the Mann-Whitney U test for comparison of groups. We will also use linear mixed model analyses on log10 transformed data for repeated measurements. Receiver operating curves and contingency tables will be used to explore sensitivity and specificity.
- Any other methods that are not planned can be considered as alternative methods.

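### Microdialysis cut-offs can only be chosen and assessed on the same 60–80 patients, so the exploratory sensitivity and specificity in section 10.3 will be biased upwards unless corrected (minor)

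*Protocol*

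**What the plan says.** Section 2.7 of the Protocol sets out the measurements: "At end of surgery totally three microdialysis catheters will be inserted". Samples are "analyzed every second hour at the bedside for glycerol, glucose, lactate, and pyruvate", and a derived measure is added: "The lactate to pyruvate ratio will be calculated". After the study, stored samples are to be "analyzed en bloc for a wide range of inflammatory mediators including complement factor 5 a and the chemokine CXCL-10"; micro-RNAs may follow.

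The same section explains why there is no decision tree: "threshold values for detecting e.g. pancreatic graft ischemia, leakages, and rejections have not been established".

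The related aims are secondary. Section 2.2 includes: "Explore if new complication specific biomarkers can be detected by the microdialysis method". Section 10.3 gives the accuracy analysis in one sentence: "Receiver operating curves and contingency tables will be used to explore sensitivity and specificity". For repeated measurements it names a signed-rank test and linear mixed models, but it gives no unit of analysis for the ROC curves or contingency tables. Sections 4 and 5 plan one cohort of 60–80 patients. No second cohort or hold-out set is described.

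**The concern.** A contingency table for a continuous marker needs a cut-off. None exists beforehand, and only one data set is described. The cut-off, and the choice of marker and catheter, must then be made on the patients who supply the reported sensitivity and specificity. Chance differences that favour the chosen combination count as accuracy. The fewer the event patients and the more combinations searched, the larger the excess.

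There is also a risk over the unit of analysis. Readings every second hour make 12 per day. Over 10 days, the median catheter life that section 2.7 reports from the liver studies, that is 12 × 10 = 120 readings per catheter and patient. If tables were built on readings, one patient's event would be counted many times and the precision would be spurious.

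At stake is the credibility of the first published accuracy figures for this method in pancreas grafts. A marker or cut-off could look promising and then fail in the next cohort.

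**Working it through.** **No figure to reproduce.** The protocol gives no sample size, event count or accuracy target for the microdialysis analysis.

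**Inputs from the protocol**
- Catheters: 3. Bedside measures: 4 analytes + 1 ratio = 5 (section 2.7). Pairs: 3 × 5 = 15, before any mediators.
- Patients: 60–80 (section 5); 70 is used as the midpoint.
- Reference rate: 0.30 for rejection and for surgical complications (section 10.2). If a whole composite were the target, event patients would number 0.30 × 60 = 18 to 0.30 × 80 = 24, or 0.30 × 70 = 21 at the midpoint.

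**Assumed inputs**
- Event counts below 18. They are plausible because section 1.1 attributes reoperations mainly to three causes (leakage, bleeding, vein thrombosis), and because catheters stay in only while they work or until discharge. An even three-way split, itself an assumption, gives 18/3 = 6 to 24/3 = 8 per type. Counts of 5, 7, 10 and 21 are shown.
- One value per patient and marker; 15 markers with no true accuracy; correlation between markers 0 or 0.5.

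**Method.** In each simulated data set, take the marker, direction and cut-off with the largest Youden index J = sensitivity + specificity − 1, and read the accuracy from the same data. The true J is 0 and the true AUC 0.50. Means over 2,000 data sets, N = 70; sensitivity, specificity and AUC are at correlation 0:

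| Event patients | Sensitivity | Specificity | AUC | J, corr. 0 / 0.5 | Chance that a marker shows both ≥ 80%, corr. 0 / 0.5 |
|---|---|---|---|---|---|
| 5 | 0.889 | 0.710 | 0.773 | 0.600 / 0.574 | 28% / 23% |
| 7 | 0.832 | 0.691 | 0.733 | 0.523 / 0.501 | 3% / 2% |
| 10 | 0.789 | 0.664 | 0.702 | 0.453 / 0.435 | 1% / 2% |
| 21 | 0.705 | 0.647 | 0.655 | 0.352 / 0.336 | 0% / 0% |

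Check of the first row: 0.889 + 0.710 − 1 = 0.599. N = 60 and N = 80 give similar results. Repeat runs gave J of about 0.55–0.60 at 5 events, 0.43–0.46 at 10 and 0.35 at 21.

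**How much is marker search, how much is cut-off search?** With 5 events and a single marker, choosing only direction and cut-off on the data still gives a mean J of 0.37. Naming the marker in advance therefore removes part of the excess, not all.

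**Does resampling cure it?** Leave-one-patient-out, repeating marker and cut-off choice each time, was run on 250 null data sets per setting (N = 70; 5, 10 and 21 events; both correlations). Mean J was between −0.05 and 0.04, so the excess disappears. The ordinary bootstrap, which subtracts average optimism, was tried on 150 of these data sets with 60 resamples each. It left J at about 0.32 with 5 events, 0.17–0.18 with 10 and 0.13 with 21. A bootstrap that tests on patients already in the resample corrects too little here.

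**Precision with the patient as unit.** Exact 95% intervals for sensitivity: 4/5 gives 28–99%, 8/10 gives 44–97%, 17/21 gives 58–95%. These intervals ignore selection, so they accompany the correction and do not replace it.

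**The case against.** The strongest reply is that nothing in section 10.3 is wrong. ROC curves are a normal exploratory tool, both microdialysis aims are worded as exploration, and section 2.7 openly says that thresholds are lacking and declines a decision tree. Cut-off rules and internal validation often sit in a statistical analysis plan, which may exist but is not shown. The protocol also has prior expectations, such as the lactate patterns and glycerol near the anastomosis in section 1.4, so the search need not treat 15 pairs alike. This stands as far as it goes and keeps the point minor. It does not remove the bias from the figures that the stated method would produce.

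Four stronger readings are tempting and are not supported:
- **The protocol commits to choosing and testing cut-offs on the same patients.** It does not say so. This is inferred from the absence of thresholds and of a second data set.
- **Tables will be built on readings.** No sentence says this, and section 10.3 recognises repeated measurements elsewhere. It is a risk only.
- **Derived thresholds would steer reinterventions.** Section 2.7 expects only that deviations may prompt examinations such as Doppler, and nothing commits to using a threshold from this study.
- **A useless marker would typically match the liver result in section 1.4.** That result exceeds 80% for both sensitivity and specificity for rejection. The typical null specificity here is about 0.65–0.71, and the chance that both reach 80% is appreciable only with about 5 events or fewer.

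**Conclusion.** The concern holds as a minor point on an exploratory secondary aim. Without prior thresholds or a validation set, the planned sensitivity and specificity will be apparent values, biased upwards. For the best of 15 uninformative markers in 70 patients the excess in the Youden index is about 0.55–0.60 with 5 event patients, 0.43–0.46 with 10, and still about 0.35 with 21.

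The size rests on assumed event counts, on one value per patient, and on an even-handed search over 15 pairs. Choosing among several summaries of the two-hourly readings, or adding the mediators, would increase it; a search narrowed by prior findings would reduce it. The direction of the bias does not depend on these assumptions.

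**What to change.** In section 10.3:
1. Make the patient the unit for ROC curves and contingency tables, with one summary per catheter and measure. Define the window identically for patients with and without the event, for example a fixed postoperative period, or a matched reference day for event-free patients. A window counted back from the event alone is undefined for the patients who supply the specificity.
2. Report AUC, sensitivity and specificity from resampling that repeats marker and cut-off selection in every round. Leave-one-patient-out is the simplest choice. If the bootstrap is used, score only patients left out of each resample. For the AUC, leave out pairs of one event and one event-free patient, since different rounds may select different markers.
3. Give exact patient-level confidence intervals and the number of event patients beside each estimate.
4. State that any cut-off awaits confirmation in new patients.

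Naming markers in advance from the group's earlier findings is optional and useful, but does not replace step 2. Lactate with an unchanged lactate/pyruvate ratio is a two-variable pattern and would need its own scoring rule.

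Cost: some analysis code and less favourable accuracy figures. No new data, patients or procedures.

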**10.4 Provisional analysis**

Summaries of provisional data will be carried out (descriptive statistics, graphs) during the course of the study when it is considered necessary, particularly with regard to the rejection rate. In any case, an intermediary/provisional analysis will be performed when the first 20 patients have completed 3 months follow-up. These summaries will be used only for control purposes and will not necessarily include formal statistical analyses.

Discontinuation of the study and our routine CS-dosing will be considered, at least at the 20 patients/3 months follow-up point of time, according to these criteria:

- If the biopsy-proven combined rejection rate (pancreas + duodenal-segment + kidney) in the study group is  doubled compared with HC.
- If the rate of surgical complications/reoperations in the study group  doubled compared with the HC.

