From late 2011 and up to date, several measures have been implemented to improve outcome and reduce the rate of surgical complications. In line with most Tx centers in Scandinavia, we have switched the prophylactic anticoagulation treatment from our traditional Macrodex® regime to a Fragmin® regime. Several surgical/technical changes have also been implemented during recent years; tentatively more atraumatic graft procurement, preserving the entire coeliac arterial axis including the gastroduodenal artery, obtaining a long portal vein to reduce the need for elongation, as well as extended in situ dissection by means of LigasureTM. Due to the conventional lack of rejection monitoring parameters, we launched an investigatory surveillance program, with protocol biopsies of the duodenal segment via double balloon enteroscopy (13). The impact and value of this program has yet to be investigated. Previous reports have described separate rejection of the pancreas or kidney in the SPK setting, and the gold standard for proving rejection of the pancreas is undoubtedly a biopsy of the pancreas itself. This encouraged us to further develop techniques for better surveillance, such as endoscopic transduodenal ultrasound-guided biopsies of pancreas (EUSBP). Inferior outcome of PTA and lack of valid tools for immunosurveillance in the absence of a simultaneous kidney graft, have led some centers to evolve the duodeno-duodenostomy (DD) for drainage of the exocrine pancreas, making the EUSBP possible. There are many theoretical advantages with the DD, especially regarding rejection surveillance, and we have recently adopted this technique. The endoscopic access afforded by the DD also makes it possible to stent the pancreatic duct in case of exocrine leakage.

Though, in recent years we have experienced a very low incidence of complications with the conventional percutaneous ultrasound-guided pancreas biopsy. In our latest, retrospective study (Horneland et al., Am J Transpl; in press), focusing on the duodenoduodenostomy, there were no complications among 18 percutaneous pancreas biopsies performed.

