**2 OBJECTIVES OF THE STUDY**

Several studies have shown acceptable results after PTx by substituting ATG with basiliximab (22-26), which is considered to convey a considerably lower number of adverse events. However, our experiences with ATG in PTx (introduced in 2004) are good, and our presumably gentle way of administrating the drug – directed by T-cell counts - is in fact unique (12). The potential advantages of reducing the overall corticosteroid (CS) load is obvious, as CS is a well-known pro-diabetic agent and causes severe long term adverse effects (22).

On this background, we have very recently reduced our CS dosing (in the routine protocol) to a level corresponding to our Kidney Tx protocol (valid since 2009). Thus*, we intend to prospectively investigate and compare a single cohort of our present PTx immunosuppressive protocol with previous (historical) cohorts.*

The rationale for the study is that; *i*) a high immunosuppressive load, and in particular CS, may be partly responsible for the high rate of PTx associated complications/reoperations; *ii*) a high immunosuppressive load is related to infectious complications; *iii*) improved PTx rejection surveillance by DD and EUSBP allows a lower-graded immunosuppressive protocol; iv) evaluating the surgical and medical measures made to our PTx program during the past two years

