**2.1** **Primary objectives**

- Compare the incidence of *acute rejection episodes* at 6, 12, 36 and 60 months after pancreas transplantation, between our single prospective cohort with lower CS vs a historic, retrospective control group (PTx performed during 2011-2013). The incidence of rejection is defined as the fraction of patients in which rejections episodes (one or more) have been proven by biopsies. For SPK rejection in eitherorgan, pancreas or kidney, counts.
- Compare the incidence of *surgical complications*, involving reoperations and reinterventions, between the prospective study group and retrospective control group.

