**2.3 Immunological studies**

- Scheduled endoscopic (EUS) biopsies will be taken according to our present routine protocol; simultaneously from these four transplant/organ sources at predestined points of time:

- Pancreas transplant (*P*)

- Kidney transplant (*K*)

- Duodenal segment of pancreas transplant (*tD*)

- Duodenum of recipient = native Duodenum (*nD*) – Serves as ‘control’

• Baseline (Day 0; at Tx): *K +tD + nD* - These will be taken during surgery

• 3 weeks post-Tx: *P +tD + nD* - Endoscopic

• 6 weeks post-Tx: *P + K + tD + nD* - Endoscopic (P/tD/nD) + Percutaneous (K)

• 12 months post-Tx: *P + K + tD + nD* - Endoscopic (P/tD/nD) + Percutaneous (K)

Within the study, we also want to take conventional percutaneous, ultrasound-guided P biopsies at 6 weeks and 12 months post-Tx – in order to compare the yield (and complications) by EUS vs percutaneous P biopsies.

In addition, indication biopsies will be taken whenever there is suspicion of rejection

in either organ. Preferably, simultaneous P + tD + nD endoscopic biopsies, P

percutaneous biopsies and K percutaneous biopsies should be obtained.

All biopsies will be examined at our local pathology unit; the pancreas and duodenal biopsies by prof. [name] and dr. [name]; the kidney biopsies by prof. [name] and dr. [name]. The pancreas and kidney biopsies will be evaluated by well-known BANFF criteria, while duodenal biopsies will be rated according to Wu et al. (27).

- Histological evaluation of the scheduled and indication biopsies will involve comparisons between biopsies from the various transplants/organs of the same patient.
  - Rejection histology scores.
  - Immunoshistochemistry on immunologic markers (CD25, FOXP3, CD4, CD3, CD8, CD45RO, perforin, granzyme A/B, etc).
    - Blood samples will be obtained at the time of transplantation and the later scheduled appointments indicated above.
  - Study of immune cell activation (CD25, FOXP3, CD4, CD3, CD8, CD45RO, perforin, granzyme A/B, etc) and cytokines (IL-2, TNF-a, IFN-g, IL-10, IL-12 etc).
  - Compare biomarkers in serum, indicative of acute rejection, by at least weekly blood sampling post-Tx (RNA microarray on a series of genes related to rejection, quantitative PCR on selected genes) (28-29).
  - Study of donor specific antigens (DSA)
    - DSA present pre-Tx (already routine)

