**10.1** **Strategy regarding 0-hypothesis**

Regarding the ‘*Incidence of rejection*’, a non-inferior approach seems reasonable. The most important aspect is to avoid the following (Type 1) error: Not detecting an elevated rejection rate in the single cohort observational study group (SCOS), when there in fact is a difference in favor of the historic, control (HC) group, with high-CS dosing.

One could argue to use a one-sided test/“rejection region”, because it is highly unlikely that the low-immunosuppressive regimen will yield a lower incidence of rejection. However, according to statistical tradition, a two-sided test will be demonstrated.

Thus, the *0-hypothesis* will have to be:

H0: *The SCOS group will have a significantly different rejection rate compared to the HC group* (*SCOS Gr.* ≠ *HC Gr.*)

- Between groups comparison of total biopsy-proven rejection rate; based on scheduled and ‘ad hoc’ biopsies from the duodenal segment, pancreas and kidney.

-- Biopsy-proven rejection in either organ (for SPK) contributes to the rejection incidence.

Regarding the ‘*Rate of surgical complications*’, the most important aspect is to avoid the following (Type 1) error: Demonstrating an elevated complication rate in the HC group, when there in fact is no difference.

Also here, one could argue to use a one-sided test/“rejection region”, because it is no reason to believe that the low-immunosuppressive regimen will yield a higher rate of complications. However, according to custom, a two-sided test will be demonstrated. Thus, a natural *0-hypothesis* will be:

H0: *The SCOS group and the HC group will have similar rates of surgical complications* (*SCOS Gr. = HC Gr.*)

- Between groups comparison of surgical complication rate; defined as the fraction of patients experiencing one or more surgical complications, involving reoperation or reintervention.

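### The interim rejection prompt and the final comparison with historic controls count rejections found on scheduled biopsies, which the controls probably had fewer of, so part of any excess may be added detection

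*Protocol*

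**What the plan says.** Section 10.4 sets the interim criterion. When the first 20 patients have 3 months of follow-up, discontinuation is to be considered if the "biopsy-proven combined rejection rate (pancreas + duodenal-segment + kidney) in the study group" is doubled relative to HC. The section calls the summaries a control measure, so the criterion prompts a discussion and is not a binding rule.

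What counts as rejection is set in section 10.1: "Between groups comparison of total biopsy-proven rejection rate; based on scheduled and" ad hoc biopsies of the duodenal segment, pancreas and kidney. Section 10.4 names the same three tissues and does not limit the count to indication biopsies.

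Section 2.3 gives the study group's schedule. Using its abbreviations (P pancreas graft, K kidney graft, tD graft duodenum), P and tD are sampled endoscopically at week 3, and P, tD and K at week 6. These are described as present routine. It then adds a further biopsy: "Within the study, we also want to take conventional percutaneous, ultrasound-guided P biopsies at 6 weeks and 12 months post-Tx".

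Section 2.1 defines the comparator as a "historic, retrospective control group (PTx performed during 2011-2013". Section 1.1 describes how surveillance changed: "From late 2011 and up to date, several measures have been implemented", and among these "we launched an investigatory surveillance program, with protocol biopsies of the duodenal segment via double balloon enteroscopy". The same section says the duodeno-duodenostomy (DD), which makes endoscopic ultrasound-guided pancreas biopsy (EUSBP) possible, was adopted only recently. It also says percutaneous biopsies were mostly avoided after the 1998 change to enteric drainage. The rationale in section 2 relies on the contrast: "improved PTx rejection surveillance by DD and EUSBP allows a lower-graded immunosuppressive protocol".

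**The concern.** A biopsy-proven rejection rate depends on how much rejection occurs and on how often tissue is taken. The study group is sampled at two fixed times inside the 3-month window, whether or not rejection is suspected. If HC patients were sampled less, the same true rejection rate would give a higher observed rate in the study group. Using the same 3-month window in both groups does not cure this, because weeks 3 and 6 both fall inside it.

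At the interim look, extra detection could be taken for a doubling under the lower corticosteroid dose. That would open a discussion about stopping the study and reversing the centre's routine dosing. The same count enters the final comparison in section 10.1, where an apparent excess could be attributed to the regimen.

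**Working it through.** **1. Scheduled graft biopsies inside the 3-month window (section 2.3).** For a recipient of a simultaneous pancreas and kidney, leaving out the day-0 samples and the native duodenum:

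- Week 3: P, tD = 2.
- Week 6: P (endoscopic), P (percutaneous), tD, K = 4.
- Total: 2 + 4 = 6, at two time points. Five are listed as present routine and one, the week-6 percutaneous P, is added by the study.

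**2. What the protocol says about HC.** No section lists the biopsies HC patients had. Four statements point to a lighter schedule for at least part of 2011-2013: the changes date from late 2011, the surveillance programme described in section 1.1 took duodenal biopsies only, DD is recent, and section 2 calls surveillance improved. This is an inference and not a documented difference.

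**3. The protocol's own figure for a doubling.** Section 10.2 gives 27 per arm for 0.30 against 0.60. Its formula gives (0.30 × 0.70 + 0.60 × 0.40) × 5.4 / 0.30² = 0.45 × 5.4 / 0.09 = 27.0, or 26.5 with c = 5.3. It reproduces. That calculation takes both rates as measured in the same way, which is the point in question here.

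**4. Effect of added detection on the interim prompt.** Inputs:

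- n = 20 (section 10.4).
- h = HC 3-month rejection rate, treated as known. The protocol gives about 30% (sections 1.3 and 10.2) without a 3-month limit, so I take 15%, 20% and 30% as assumptions.
- d = share of patients with rejection seen only on the added biopsies. It is not in the protocol; 0%, 5% and 10% are assumptions.
- No true difference between the groups.

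The trigger count is 20 × 2h, and the chance of reaching it is P(X ≥ trigger) with X ~ Binomial(20, h + d).

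| h | Trigger | Expected, no difference | Extra needed | d = 0 | d = 5% | d = 10% |
|---|---|---|---|---|---|---|
| 15% | 6/20 | 3 | 3 | 6.7% | 19.6% | 38.3% |
| 20% | 8/20 | 4 | 4 | 3.2% | 10.2% | 22.8% |
| 30% | 12/20 | 6 | 6 | 0.5% | 2.0% | 5.7% |

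**5. Check with another definition of extra yield.** Let s be the share of otherwise rejection-free patients found positive only on an added biopsy, so the observed rate is h + (1 − h)s. At s = 10% the chances are 32.3%, 17.1% and 3.1% for h = 15%, 20% and 30%. The pattern is the same: small at 30%, appreciable at lower HC rates.

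**The case against.** The strongest counter-case has four parts.

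- **The HC schedule is not documented.** Most of the study schedule is present routine. Section 1.1 already reports 18 percutaneous pancreas biopsies in a retrospective series on DD, so pancreas biopsy and DD both predate this study. Later HC patients may have been sampled much like study patients. This stands, and it is why the difference can only be called probable and its size unknown.
- **Only one biopsy is clearly study-only.** It is taken at the same visit as three other graft biopsies and samples an organ already sampled by endoscopy. The endpoint is counted per patient, so it adds a case only when the others are negative. This also stands. The count of six is not a measure of extra yield.
- **The consequence is limited.** Discontinuation is only considered, and the investigators will know which biopsy showed each rejection. This is true, but nothing in section 10.4 asks for that information to be set beside the ratio.
- **An indication-only trigger could do harm.** Section 10.1 says the error to avoid above all is missing a raised rejection rate. Rejections found and treated at a scheduled biopsy may never lead to an indication biopsy. This stands and rules out replacing the trigger.

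A reader might also infer that section 10.4 is wider than the primary endpoint, because section 2.1 says rejection in "pancreas or kidney, counts" while section 10.4 adds the duodenal segment. The text gives this little support. Section 10.4 matches section 10.1, and section 2.3 describes tD as part of the pancreas transplant.

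**Conclusion.** The point holds as a comparability weakness. By sections 10.1 and 10.4, rejections from scheduled biopsies count, study patients have such biopsies at weeks 3 and 6, and nothing allows for lighter sampling in HC. Part of any excess over HC, at the interim look or the end, may therefore be added detection.

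The size cannot be fixed from the protocol. At an assumed HC 3-month rate of 30%, a 5-10% extra yield raises the chance of a false doubling from 0.5% to 2-6%. At an assumed 15%, it rises from 7% to 20-38%. The upper figure needs both a low HC rate and a 10% extra yield, and should not be read as an estimate for this trial.

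Two stronger readings are not supported. One is that HC had no scheduled biopsies: section 1.1 describes a duodenal programme that may cover much of the HC period. The other is that a known number of HC patients preceded that programme: late 2011 dates the measures as a group, the programme has no start date of its own, and the 2013 volume is not given.

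This is a worthwhile, inexpensive improvement and not a fault that invalidates the plan.

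**What to change.** In section 10.4, keep the combined rate over pancreas, duodenal segment and kidney as the safety trigger, and add that:

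- it is computed from day 0 to day 90 in both the first 20 study patients and HC;
- the HC day-90 rate and the resulting trigger count out of 20 are tabulated before the interim look;
- beside it are shown, for each group, the patients with rejection proven on an indication pancreas or kidney biopsy, the patients with rejection seen only on scheduled or duodenal biopsies, and the number of biopsies per patient;
- a doubling is read against that split before discontinuation is considered.

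In section 10.1, add the comparison restricted to indication biopsies as a sensitivity analysis of the final result.

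The cost is a few sentences and one tabulation of HC biopsy records. It needs no new visit, biopsy, interim look or primary test. The indication-only count can understate rejection in the study group, so it should stand beside the combined trigger and not replace it.
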